### Aims and design

The primary aim of our study is to investigate the effect of a smartphone app combined with game elements on the level of physical activity of adults and older adults, measured by the average number of daily steps. The secondary aims are (1) to verify the effects of the intervention on cardiometabolic and cardiovascular health, lung function, and cardiorespiratory fitness; and (2) to verify the relationship between age group and the response rate.

We will conduct a Sequential Multiple Assignment Randomized Trial (SMART). This study was approved by the Ethics Committee of the Federal University of Sao Paulo (# 0499/2018) and is registered in the Brazilian Clinical Trials Registry (RBR-8xtc9c).

The SMART design has been recommended over the classical randomized controlled trial for technology-based interventions [12, 13] as it allows adaptations over time based on the participants’ response to the intervention. Despite the large potential and shown feasibility [14], the SMART design has, thus far, hardly been conducted in smartphone and gamified interventions.

The adaptive intervention protocol will last 6 months. Initially, participants will be randomized into one of three groups (group 1: app + tailored messages; group 2: app + tailored messages + gamification I; control group: physical activity counseling) (Fig. 1). Over 12 weeks, we will record the average number of steps per day for each participant from groups 1 and 2. At 6 weeks from initiation, participants will be classified into responders and non-responders according to the targeted average number of daily steps; all those considered as non-responders will be re-randomized, with the chance to participate in a third group – group 3: app + tailored messages + gamification II (Fig. 1). At the end of the 12 weeks, participants will continue using the app but will no longer receive any direct intervention from investigators. All participants, including those in the control group, will be reassessed at 3 and 6 months from baseline. The protocol timeline is shown in Fig. 2.

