### Interventions

#### Group 1 – App + tailored messages

Participants will use the app to track the number of daily steps and they will receive weekly text messages on their smartphones, with information about their performance on last week and motivational phrases according to their behavior-change status at the end of the protocol, the responders of Group 1 will end up in the subgroup A, while non-responders will end up in the subgroups B or C.

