#### Group 2 – App + tailored messages + gamification I

Additionally to monitoring the number of steps and individual messages, participants will be encouraged to join virtual challenges; for each challenge they complete, a virtual badge will be given. The challenges available will be related to the target number of steps per day, target distance walked in the month, and group competitions where the total number of steps is compared among the different groups of app users. Further, there will be rankings of the number of steps among all users at the end of the protocol, the responders of Group 2 will end up in the subgroup D, while non-responders will end up in the subgroups E or F.

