### Defining responders and non-responders

The American College of Sports Medicine recommendations about the quantity and intensity of physical activity suggest increases of 2000 steps per day to achieve improvements in cardiovascular health [15]. After a pre-test with persons from researchers’ networks using a smartphone app with a pedometer, we observed that the target of increasing 2000 steps/day would not be realistic to our population. Therefore, we decided to plot the average number of steps of participants in a graph using a linear tendency line and participants that present a positive slope, i.e., a tendency to increase step counts, will be considered as responders. Consequently, participants with a zero or negative slope, i.e., a tendency to maintain or decrease step counts, will be considered as non-responders. Additionally, we will use the app’s first-week step count as a reference for both sending the tailored messages and analyzing participants’ slopes. Thus, we believe that this way we will be able to set individualized and feasible goals for our population.

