#### Intermediate assessment

The intermediate assessment to identify responders and non-responders will take place at week 6 from the beginning of the protocol. We will calculate the average number of steps/day from weeks 1 to 6, and compare with the number of steps/day from the initial assessment. Participants identified as non-responders will then be re-randomized and will receive instructions about the new phase of intervention (Fig. 1). We will collect the average number of steps per day using the app interface; all participants will use the app for 1 week after randomization prior to any intervention and we will consider the step count from the first week as a comparator for weekly and intermediate assessments.

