### Data analysis

Participants’ characteristics will be presented by descriptive statistics. We will use ANOVA tests to compare the effect of interventions on the increase of physical activity levels, cardiovascular and metabolic health, lung function, and cardiorespiratory fitness among groups A + B + C and D + E + F pre- and post-intervention compared to the control group. Additionally, we will use the same test to analyze the effect of interventions on the average number of daily steps comparing the final subgroups (A to F) against the control group as well as the subgroups A + F, B + D and C + E against the control group.

To analyze the relationship between age and the response rate to each intervention, we will group responders and non-responders according to age ranges (20–30 years old, 31–40, 41–50, 51–60, 61–70, and 71 and older) and compare them in subgroups from A to F using Pearson or Spearman correlations (according to data distribution).

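### The additional tests of subgroups A to F against control compare people sorted by their own week-6 step response with an unselected group, and no stated effect contrast uses the second randomisation

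*Protocol article*

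**What the plan says.** The primary aim in Aims and design is an effect on physical activity "measured by the average number of daily steps".

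The sorting into subgroups happens after randomisation:
- In Defining responders and non-responders, "participants that present a positive slope, i.e., a tendency to increase step counts, will be considered as responders"; a zero or negative slope makes a non-responder.
- Intermediate assessment describes the check differently: "We will calculate the average number of steps/day from weeks 1 to 6, and compare with the number of steps/day from the initial assessment".
- In Group 1, "the responders of Group 1 will end up in the subgroup A, while non-responders will end up in the subgroups B or C". In Group 2, "the responders of Group 2 will end up in the subgroup D, while non-responders will end up in the subgroups E or F".
- In Aims and design, "all those considered as non-responders will be re-randomized". App steps over the 12 weeks are recorded for groups 1 and 2 only, so control has no such classification.

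Data analysis then states two sets of effect comparisons. The first is by ANOVA "among groups A + B + C and D + E + F pre- and post-intervention compared to the control group", across all outcome domains. The second, introduced as additional, is on daily steps, "comparing the final subgroups (A to F) against the control group", together with A+F, B+D and C+E against control. The strategies A+B, A+C, D+E and D+F appear only under Sample size, for sizing the later trial.

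**The concern.** A and D contain only people whose steps tended to rise in the first weeks. B, C, E and F contain only people whose steps did not. Control contains both kinds, unseparated. A difference between any one subgroup and control therefore mixes what the intervention did with who was selected into the subgroup. The protocol nevertheless presents the result as an effect of the interventions on the primary outcome variable.

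Two things are at stake. Selection may be reported as benefit in responders and as futility or harm in non-responders. And the comparison that the second randomisation protects, between the options offered to non-responders of the same first-stage arm, is not among the stated effect contrasts, although that question is a main reason for using a SMART.

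**Working it through.** **Inputs from the protocol (Sample size).** Non-response q = 50%, range 35% to 65%; 14 per arm; at least m = 3 per non-responder subgroup; probability k of 80% to 90%. The stated 42 can be reproduced: the chance of at least 4 × 3 = 12 non-responders among 28 at q = 0.5 is 0.828 (0.779 among 27), and a third arm of 14 gives 42. The point does not depend on this figure. Expected cell sizes are 14 × 0.5 = 7 in A or D and 7/2 = 3.5 in each of B, C, E and F.

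**Inputs assumed.** The protocol gives no SD, correlation or test level. I take a two-sided 5% level and no treatment effect, and let rho be the correlation between the week-6 response score and the later change in steps.

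**Bias in SD units.** For a bivariate normal pair with responders above the cut-point z for which Φ(z) = q:
- responders minus control = rho × φ(z)/(1 − q)
- non-responders minus control = −rho × φ(z)/q

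| q | A, D | B, C, E, F |
|---|---|---|
| 35% | +0.57 rho | −1.06 rho |
| 50% | +0.80 rho | −0.80 rho |
| 65% | +1.06 rho | −0.57 rho |

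At q = 50% this is ±0.24 SD for rho = 0.3, ±0.40 for 0.5 and ±0.56 for 0.7.

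**Pooled sets at q = 50%.** A+F and B+D each hold two responders for every non-responder: (2 × 0.80 − 0.80) rho / 3 ≈ +0.27 rho. C+E holds only non-responders: −0.80 rho.

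**Bias in steps per day.** Suppose the slope rule applies and each person has a linear drift with 12-week SD D, with independent weekly app noise of SD s. The true weekly slope has SD D/12. The error of a six-week fitted slope has SD s/√17.5. Then bias = 0.798 × D × (D/12)/√[(D/12)² + s²/17.5]. With s = 1,000:
- D = 0: 0
- D = 500: 0.798 × 500 × 41.7/242.6 ≈ ±69
- D = 1,500: 0.798 × 1,500 × 125/269.8 ≈ ±555
- D = 2,000: 0.798 × 2,000 × 166.7/291.4 ≈ ±913

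**Dependence on the responder rule.** In a weekly-step model with no effect (assumed week-to-week SD 1,500), the responder bias in month-3 minus baseline accelerometer steps was as follows. Under the slope rule it was 0.00 SD with independent weekly noise, 0.19 to 0.39 SD with autocorrelation 0.5 to 0.9, and 0.11 to 0.30 SD with personal trends. Under the rule in Intermediate assessment it was 0.42 to 0.55 SD.

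**False positives by simulation, no effect, q = 50%.**

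| | A vs control | C+E vs control | seven-group ANOVA |
|---|---|---|---|
| rho 0.3, 14 per arm | 7.6% | 7.3% | 11.1% |
| rho 0.5, 14 per arm | 11.6% | 12.2% | 24.4% |
| rho 0.3, 100 per arm (illustrative) | 27% | 27% | 70% |

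**Contrasts that keep randomisation.** In the same simulations, A+B+C and D+E+F against control, and B against C, had bias near 0 and error rates of 4% to 6%. Strategy A+B, with A weighted 1 and B weighted 2, had bias near 0: 0.5 × 0.80 rho − 2 × 0.25 × 0.80 rho = 0.

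**Labels.** Under Sample size, B switches to group 2, C to group 3, E to group 1 and F to group 3. B+D then shares a final treatment (group 2), but A+F and C+E do not; they would if E and F were exchanged. None of the three sets is a strategy named under Sample size.

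**The case against.** The strongest reply is that the protocol already has a valid effect analysis. The whole-arm comparison is listed first, covers every outcome domain and keeps the randomisation; the A to F tests are extra. That stands, and a reader who inferred that the trial's effect analysis as a whole is invalid would be wrong.

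A reader might also infer that A and D must look beneficial, and the rest useless, whatever the interventions do. The documents do not support this. The bias needs early response to correlate with later change, and it is zero in the case of no personal drift and independent weekly noise under the slope rule. Nor is the comparison strictly circular: response is read from app steps by week 6, whereas a comparison with control, which has no 12-week app record, would presumably rest on the accelerometer at 3 or 6 months. The two measures are related but not identical.

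It is likewise too much to say that the second randomisation will never be analysed. A separate analysis plan may add such contrasts. What can be said is that none of the effect contrasts stated here uses it.

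Finally, Sample size describes feasibility as the main objective, and single-test inflation at 14 per arm is modest. But the primary aim is worded as an effect, the Discussion expects adequate power for some variables, and the bias in the estimate does not shrink as the sample grows.

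**Conclusion.** The point holds in a limited form. The additional comparisons of A to F, A+F, B+D and C+E with control are not randomised and can show differences without any treatment effect: upward for A and D, downward for B, C, E, F and C+E, and slightly upward for A+F and B+D. The direction follows from the protocol's own definitions, given a positive correlation between early response and later change.

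The size rests on assumptions: about ±0.80 × rho SD at 50% non-response or, in the drift model, from 0 to about ±550 steps/day (drift SD 1,500) and about ±900 (drift SD 2,000). It also depends on which of the two responder rules is used. In the pilot the main damage is a misleading estimate; in a larger trial with the same analysis, false positives would become frequent. The comparison of whole first-stage arms with control is unaffected. Because the Data analysis section itself fixes these contrasts, this is a fault in what is stated and not a detail left to another document.

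**What to change.** In Data analysis:
1. Keep A+B+C and D+E+F against control as the effect analysis.
2. Report A to F, A+F, B+D and C+E descriptively, without tests against control.
3. Add the randomised contrasts among non-responders: B vs C within group 1 and E vs F within group 2, as estimates with confidence intervals.
4. Compare the strategies A+B, A+C, D+E and D+F with control, weighting re-randomised non-responders by 2 and responders by 1. These weights assume equal allocation at the second randomisation, which should be stated. Use robust standard errors.

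Two contradictions must be settled first. The E and F labels in Sample size and the pooling in Data analysis have to be reconciled before any gamification II cells are pooled. The responder rules in Defining responders and non-responders and in Intermediate assessment have to be reconciled too, since they can sort the same person differently.

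The cost is a change of wording; no data collection changes. The price is fewer tests against control, and second-stage contrasts that are very imprecise in the pilot, with about 3 people per cell.

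### Eleven planned comparisons share one control group, none is named as the answer to the primary aim, and only two compare groups as first randomised

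*Protocol article*

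**What the plan says.** Aims and design sets the primary aim: "The primary aim of our study is to investigate the effect of a smartphone app combined with game elements". The outcome is physical activity, taken as mean steps per day. This fixes an outcome but not a comparison.

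Data analysis then gives three sets of comparisons with the control group:

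- **Pooled first-stage arms**, on physical activity and the other health domains: "among groups A + B + C and D + E + F pre- and post-intervention compared to the control group".
- **Final subgroups**, introduced as an addition and on average daily steps: "comparing the final subgroups (A to F) against the control group as well as the subgroups" that the next item lists.
- **Further pools**, also on daily steps: "as well as the subgroups A + F, B + D and C + E against the control group".

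The test is ANOVA throughout ("We will use ANOVA tests to compare the effect of interventions on the increase of physical activity levels", with the same test for the additions). The section gives no alpha, no sidedness and no primary contrast.

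Subgroup membership depends on response. Under Defining responders and non-responders, a positive step-count slope makes a participant a responder (A or D). A zero or negative slope leads to re-randomisation (B or C, E or F).

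**The concern.** Daily steps is the primary outcome, and the plan offers many routes to a positive result on it. If no contrast is fixed in advance, whichever of the eleven reaches significance can be presented as the app working.

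There is a second and separate problem. Nine of the contrasts set groups selected on step-count slope, or pools of such groups, against a control group that was not selected. A responder subgroup can then look better than control, and a non-responder subgroup worse, with no treatment effect at all. Adjusting for multiplicity does not remove that bias.

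**Working it through.** **1. Count.** Pooled arms 2 (A+B+C, D+E+F), single subgroups 6 (A to F), further pools 3 (A+F, B+D, C+E): 2 + 6 + 3 = 11. The last nine are explicitly on daily steps. The first two cover physical activity, which the primary aim measures by daily steps.

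**2. Which contrasts are randomised comparisons.** A+B+C is all of group 1 and D+E+F is all of group 2, so these two keep the first randomisation. The Sample size section lists the adaptive strategies as A+B, A+C, D+E and D+F. None of A+F, B+D or C+E is among them. On that section's labels (C and F switch to group 3, E switches to group 1), A+F and C+E each mix group 1 and group 3 treatment.

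**3. The plan's own figure.** The Sample size section gives 42 participants, 14 per arm, from q = 50%, m = 3 per non-responder subgroup and k of about 80 to 90%. With a balanced split, three in each subgroup needs at least 6 non-responders in an arm: P(X ≥ 6 | n = 14, q = 0.5) = 0.788. This reproduces 14 to within about one point of 80%, read per arm. The expected size of B, C, E and F is 14 × 0.5 / 2 = 3.5.

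**4. False-positive rate under no effect.** Inputs: 14 controls, subgroup sizes 7/4/3 and 7/3/4, normal outcomes, two-sided tests. Alpha is an assumption, because the article states none. Simulation of 200,000 trials, with the shared control and overlapping groups built in:

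| Reading of the plan, alpha 0.05 | P(at least one false positive) |
|---|---|
| Eleven pairwise t-tests, no gate | about 28% |
| Three omnibus ANOVAs | about 10.5% |
| Contrasts read only after a significant F in their family | about 9% |
| First two contrasts only, pairwise | 9.0% |

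The pairwise figure is 27.7 to 27.8% across splits corresponding to q = 35 to 65% (28.1 to 28.3% by normal theory). It depends strongly on the assumed per-test alpha:

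| Per-test alpha | Eleven pairwise | F-gated |
|---|---|---|
| 0.01 | 7.1% | 1.8% |
| 0.025 | 15.8% | 4.5% |
| 0.05 | 27.7% | 9.0% |
| 0.10 | 46.8% | 18.2% |

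For reference, eleven independent tests would give 1 − 0.95^11 = 43.1%. The true figure is lower because the tests are positively correlated.

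**5. Responder selection.** Step 4 treats A to F as random subsets, which they are not. Suppose there is no treatment effect and the outcome is Y = ρS + √(1 − ρ²)e, with S the standardised slope and responders those with S > 0. The expected difference from control is then ρ√(2/π) = 0.798ρ SD for responders and −0.798ρ SD for non-responders. The correlation ρ is not in the article, so a range is shown:

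| Assumed ρ | Built-in shift (SD) | Any of eleven, pairwise | F-gated |
|---|---|---|---|
| 0.2 | 0.798 × 0.2 = 0.16 | about 31% | about 11% |
| 0.4 | 0.798 × 0.4 = 0.32 | about 40% | about 19% |
| 0.6 | 0.798 × 0.6 = 0.48 | about 53 to 54% | about 36% |

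**The case against.** The case for leaving the plan alone has real substance.

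- **ANOVA is named, not pairwise t-tests.** This stands. A reader might infer that 28% is the plan's error rate, but it applies only if every contrast is tested pairwise without a gate. The wording of comparisons against control leans that way without settling it, and the omnibus or gated reading gives about 9 to 11%.
- **No alpha is stated.** This stands too. A reader might set 28% against a promised 5%, but the article promises no 5%.
- **Silence on adjustment is not a statement that none will be made.** A condensed article commonly leaves multiplicity procedures to an analysis plan, which is not shown here. It would be wrong to say that the comparisons are unadjusted. An adjustment would still not name the primary contrast, nor undo selection by response.
- **There is some ordering.** The pooled arms come first and the rest are additions, so the eleven are not presented as strictly equal. But this is no formal hierarchy, and two pooled arms remain with neither ranked first.
- **The visit can be inferred.** Direct intervention ends at 3 months, so post-intervention most naturally means then. Against that, Aims and design says the adaptive protocol lasts 6 months, with reassessment at both 3 and 6 months.
- **It is a pilot.** The figure of 14 per arm is the pilot size only, and the Sample size section puts feasibility ahead of effects. A reader might infer that subgroups of 3 or 4 describe the whole trial; the article does not say so. Yet Data analysis is not limited to the pilot, and the Discussion speaks of testing effectiveness with sufficient power for some key variables.
- **The further pools may follow the treatment finally received.** That would fit if E and F were swapped relative to the Sample size section. Even then, they would join responders of one arm to non-responders of the other, which is not a comparison of groups as randomised.

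**Conclusion.** The point holds in limited form. Eleven comparisons with one control group are written down and none is designated as answering the primary aim. Nine of them rest on groups selected or re-pooled by response, three of which match no adaptive strategy in the Sample size section.

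At an assumed 0.05 two-sided and the pilot size, the chance of at least one false positive is up to about 28% with ungated pairwise testing, and about 9 to 11% with omnibus or F-gated ANOVA. At that alpha, every reading checked exceeds 5%. These figures ignore responder selection, which takes the pairwise figure to about 31 to 54% over the assumed correlations. For that reason the 43% from independent tests should not be taken as an upper bound for this design.

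The documents do not support a single error rate for the plan, or the statement that no adjustment will be applied.

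**What to change.** In Data analysis, name one primary contrast between groups as randomised, at one visit. For example: D + E + F against control, accelerometer steps per day at 3 months, adjusted for baseline accelerometer steps. The accelerometer is the natural measure, because the app is installed only for groups 1 and 2. State the alpha. Test A + B + C against control second, in fixed sequence, or handle the two together by Dunnett.

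The example is not a perfect match to the aim. On the Sample size section's labels, E has moved to group 1 at week 6, so D + E + F includes people no longer on gamification. The contrast estimates the effect of starting in group 2, and the text should say so.

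Report A to F singly, A + F, B + D, C + E and the 6-month visit as exploratory estimates with 95% confidence intervals and no significance claim. State that the subgroups are defined by response and are not randomised comparisons with control.

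The cost is a few sentences and no new data. The downside is fewer contrasts that can be called significant.

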#### Group 3 – App + tailored messages + gamification II

The second stage of gamification will be available in the protocol by the time of the intermediate assessment (6th week of intervention). Gamification II will include the same features of gamification I, plus opportunities for socialization among participants (biweekly group meetings) and discussion forums about physical activity.

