### Sample size

The main objective of a SMART study relies on the feasibility of carrying out a future large-scale trial, rather than investigating the effects of the proposed set of treatments. To reach this goal, we must ensure that the number of subjects will be sufficient and balanced among all of the subgroups. According to Almirall et al. [16], a fixed probability *k* of about 80–90% should be considered so that at least *m* participants would end in non-responders’ subgroups B, C, E and F (Fig. 1). Considering a range of non-response rates in SMART studies of 35–65%, we calculated an *m* of 3 participants per subgroup as sufficient to ensure familiarity with the protocol, treatment delivery, and identification of potential problems. For a non-response rate of q = 50% at the end of the 6th week, our pilot SMART study will require 42 participants (14 per arm) [16].

After conducting this SMART pilot, we will consider the variation on the average number of steps per day to calculate the sample size of the trial, including an up to 40% loss to follow-up and a less optimistic non-response rate of 65%. To increase the feasibility of a future large-scale trial, we will calculate the sample size considering groups A + B (maintain – switch to group 2), groups A + C (maintain – switch to group 3), groups D + E (maintain – switch to group 1), groups D + F (maintain – switch to group 3), and the control group.

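### The pools A + F, B + D and C + E conflict with the protocol's own codes for E and F and, under either labelling, select on response and match none of its four adaptive strategies

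*Protocol article*

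**What the plan says.** The Protocol article defines the final subgroups in stages.

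- **Response status.** The Group 1 section says "the responders of Group 1 will end up in the subgroup A, while non-responders will end up in the subgroups B or C". The Group 2 section says "the responders of Group 2 will end up in the subgroup D, while non-responders will end up in the subgroups E or F".
- **Second-stage treatment.** Sample size gives the switches as "groups A + B (maintain – switch to group 2), groups A + C (maintain – switch to group 3") and "groups D + E (maintain – switch to group 1), groups D + F (maintain – switch to group 3"). These four pairs, with the control group, are to be the basis for sizing the later trial.
- **Content of group 3.** "Gamification II will include the same features of gamification I, plus opportunities for socialization among participants".
- **Analysis.** Data analysis first compares A + B + C and D + E + F with control by ANOVA. It then uses the same test, for daily steps, on each final subgroup A to F against control, "as well as the subgroups A + F, B + D and C + E against the control group". It does not say what these three pools stand for.

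Sample size plans 14 participants per arm "For a non-response rate of q = 50% at the end of the 6th week", within a range of 35% to 65%.

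**The concern.** A sequential trial of this kind yields strategies of the form: start on one treatment, stay if responding, switch to a named alternative if not. The protocol lists four such strategies when it discusses sample size. It then plans tests on three pools that are not among them, and two of those pools do not even share a final treatment under the protocol's own codes.

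Two things are at stake. First, an analyst who follows both sections literally will report contrasts whose meaning depends on which section is right about E and F. Second, membership of each pool depends on what happened after randomisation, whereas the control group is taken whole. A difference from control can then arise with no treatment effect, and a real effect can be inflated or hidden.

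**Working it through.** **Step 1. Map the codes.** Response status comes from the Group 1 and Group 2 sections, and final treatment from Sample size. The last column exchanges E and F.

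| Subgroup | First stage | Week 6 | Final treatment as coded | With E and F exchanged |
|---|---|---|---|---|
| A | group 1 | responder | 1 | 1 |
| B | group 1 | non-responder | 2 | 2 |
| C | group 1 | non-responder | 3 | 3 |
| D | group 2 | responder | 2 | 2 |
| E | group 2 | non-responder | 1 | 3 |
| F | group 2 | non-responder | 3 | 1 |

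**Step 2. Read the pools.**

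| Pool | Final treatments as coded | With E and F exchanged | One of the four strategies? |
|---|---|---|---|
| A + F | 1 and 3 | 1 and 1 | no |
| B + D | 2 and 2 | 2 and 2 | no |
| C + E | 3 and 1 | 3 and 3 | no |

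As coded, two of the three pools mix different final treatments. With E and F exchanged, the three pools mean ended on group 1, 2 and 3 respectively. Under either reading each pool crosses the two first-stage arms, and none is a strategy.

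**Step 3. Responder share of each pool.** Inputs: non-response rate q (50%, range 35% to 65%) and 14 per arm, both from Sample size. Assumptions: the same q in both arms, and 1:1 re-randomisation.

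At q = 50%, the expected numbers are A = D = 14 × 0.5 = 7, and B = C = E = F = 14 × 0.5 / 2 = 3.5.

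- A + F: 7 / (7 + 3.5) = 0.667
- B + D: 7 / (3.5 + 7) = 0.667
- C + E: 0 / (3.5 + 3.5) = 0
- An unselected arm: 1 − q = 0.50

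In general the share for A + F and B + D is s = (1 − q) / [(1 − q) + q/2]. Relabelling to A + E, B + D and C + F changes nothing here: the first two pools still join one responder cell to one non-responder cell, and the third still joins two non-responder cells.

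**Step 4. Bias with no treatment effect.** Let g be the mean outcome of responders minus that of non-responders. Randomisation gives control the same expected mix of would-be responders, 1 − q. A pool with responder share s therefore differs from control by (s − (1 − q)) × g.

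| q | s for A + F, B + D | 1 − q | Bias, A + F and B + D | Bias, C + E |
|---|---|---|---|---|
| 35% | 0.788 | 0.65 | +0.138 g | −0.65 g |
| 50% | 0.667 | 0.50 | +0.167 g (1/6) | −0.50 g (1/2) |
| 65% | 0.519 | 0.35 | +0.169 g | −0.35 g |

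**Step 5. Check the replacement.** A strategy such as A + B, pooled without weights at q = 50%, would also hold 7 / 10.5 = 0.667 responders. Giving non-responders weight 2 restores the balance: 7 / (7 + 2 × 3.5) = 0.50, the unselected share.

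**The case against.** The best defence is that this is a two-letter slip in a secondary analysis. Exchange E and F in one section and all three pools become coherent by final treatment. B + D already agrees with the codes and can be read descriptively as those who ended on group 2. The first-listed comparisons, A + B + C and D + E + F against control, use arms as first randomised and serve the primary aim. The Sample size section also says that the main objective of a SMART study is feasibility for a future large trial, and the four strategies are named there for sizing, not as an aim.

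Most of this stands, and it limits the harm. It rules out three stronger readings that a reader might take:

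- That none of the pools can be interpreted. B + D has a clear descriptive meaning; what it lacks is an unbiased contrast with control.
- That the mixed pools combine opposite treatments. Group 3 contains the app and messages of group 1, so the treatments are different, not opposite.
- That the primary aim goes unanswered. The whole-arm comparisons address it.

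The defence does not cover selection on response, which Step 3 shows to be the same after relabelling. Nor is this a detail left to an analysis plan: the article itself names the contrasts to be tested.

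It is also fair to object that the 1:1 ratio is not stated. The blocks of six describe the first allocation to three groups, and no ratio is given for the second. The exact fractions depend on it. The direction does not: C + E has no responders at any ratio, and A + F and B + D exceed the unselected share whenever only part of the relevant non-responders enters the pool.

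**Conclusion.** The concern holds, as a should-fix. Sample size and Data analysis cannot both be right about E and F if the pools are meant to share a final treatment. A reader might infer that Data analysis is the section in error, but the text supports an exchange in either place, and Fig. 1 is not reproduced in the text I worked from.

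Whichever label is right, none of the three pools gives an unbiased comparison with control, and no planned test covers the four strategies that the protocol names. At q = 50% the null bias is about +1/6 of the gap for A + F and B + D and −1/2 for C + E. This rests on 1:1 re-randomisation and equal q in both arms; the signs also require responders to do better than non-responders at follow-up.

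A reader might want the bias in steps per day. The document gives no standard deviation and no expected gap between responders and non-responders, so any such figure would rest on assumed values. The fractions are what can be supported.

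**What to change.** 1. Reconcile E and F across Sample size, Data analysis and Fig. 1.
2. In Data analysis, replace A + F, B + D and C + E with A + B, A + C, D + E and D + F, each against control. These are the same four sets of people whichever way E and F are settled; only the treatment names attached to D + E and D + F change.
3. State the re-randomisation ratio, and weight participants by the inverse of their actual re-randomisation probability: 1 for responders, and 2 for non-responders if the ratio is 1:1. Replicate responders so that they count in both strategies that begin with their arm, and use robust standard errors, with a small-sample correction at pilot size.
4. Report any comparison by final treatment, and the single-subgroup comparisons A to F in the same sentence, as descriptive only, since they select on response in the same way.
5. Leave the A + B + C and D + E + F comparisons as they are.

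The cost is a sentence of text and standard regression code, with no new data or participants. With about 3.5 people expected in each re-randomised cell, the pilot estimates will be imprecise.
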